### Outcome measures

#### Primary outcomes

Primary outcomes will include self-reported measures of affect, appraisals of task-related stress, trait and state rumination, as well as trait and state self-compassion. Further primary outcomes will be response and habituation indices of biological stress measures for HPA axis, autonomic, and inflammatory responses (i.e., cortisol, sAA, HR, HRV, plasma IL-6, cytokine expression rates of IL-6, IL-1β, NF-кB, IкB). To obtain response indices, delta scores will be computed for the initial and repeated exposure to stress using peak values relative to baseline (e.g., peak cortisol values at + 1, + 10, or + 20 min post-TSST minus cortisol values at –1 min pre-TSST). To obtain habituation indices of biological stress measures, values of the second stress response will be subtracted from the first stress response values.

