### Power analysis

An a priori power analysis has been conducted using G*Power (version 3.1.9.6) for sample size estimation, based on the findings of a preliminary study [20]. The analysis is limited to the reference biomarkers cortisol and sAA, as no available data provide insights into the modifiability of inflammatory response patterns.

As demonstrated in the aforementioned preliminary study [20], the findings suggest a high modifiability of cortisol and sAA responses through the manipulation of psychological coping mechanisms. Specifically, a large effect was observed in the difference in cortisol response habituation between intervention and control group (*d* = 0.81), while a moderate-to-large effect was found for the difference in sAA response habituation (*d* = 0.67). Based on these findings, medium-to-large effects are expected for differences between experimental groups with regard to their difference in habituation of biological stress system activity. Power analyses revealed a sample size of *N* = 111 (*n* = 37), using an effect size of *f*^2^ = 0.30, *α* = 0.05, 1-*β* = 0.80, number of groups = 3. To address the anticipated 10% dropout rate caused by non-appearance of participants on study day 2 or insufficient biological sample volumes, an additional nine participants (three per condition) will be recruited and tested in this study, resulting in a total sample size of *N* = 120.

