#### Rumination

Trait rumination will be assessed using a German version of the Response Style Questionnaire [RSQ, 42] from Kühner, Huffziger, and Nolen-Hoeksema [43]. The scale evaluates how participants typically respond to depressive mood and includes two subscales Rumination (21 items) and Distraction (11 items). Items on the Rumination scale depict reactions focusing on depressive mood, its causes, and consequences (e.g., “Think about how alone you feel”), while items on the Distraction scale describe active and problem-solving approaches to reduce feelings of depression (e.g., “Help someone else with something in order to distract yourself”). Ratings will be recorded on a 4-point Likert scale ranging from “almost never” to “almost always,” with nine negative items being reverse-coded. Subsequently, scores will be computed by summing up all items for each response style.

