#### Self-compassion

To assess trait self-compassion, a German version of the Self Compassion Scale [SCS, 28] from Hupfeld and Ruffieux [SCS-D, 27] will be utilized. The scale comprises 12 items addressing self-kindness (e.g., “I try to be loving towards myself when I’m feeling emotional pain.”), self-judgment (e.g., “I’m disapproving and judgmental about my own flaws and inadequacies.”), perceptions of common humanity (e.g., “When things are going badly for me, I see the difficulties as part of life that everyone goes through.”), perceptions of isolation (e.g., “When I think about my inadequacies, it tends to make me feel more separate and cut off from the rest of the world.”), mindfulness (e.g., “When something upsets me I try to keep my emotions in balance.”), and over-identification (e.g., “When I’m feeling down, I tend to obsess and fixate on everything that’s wrong.”). Ratings will be made on a 5-point Likert scale ranging from “almost never” to “almost always”. Following reverse-coding of items assessing perceptions of self-judgment, isolation, and over-identification, total sum scores will be computed.

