### Data preparation and statistical analysis

Data preparation and statistical analysis will be performed using IBM SPSS Statistics 26 (IBM Corp., Armonk, NY, USA). Following our pre-registered analysis plan [60], data will be screened for outliers using *z*-scores, and outliers which differ more than 3 standard deviations from the participants’ mean will be excluded from further analysis. In addition, participants will be excluded in case of elevated cortisol levels (e.g., > 12 nmol/L or *z* > 3.29) after arrival at the laboratory (i.e., at baseline) and after accommodating to the testing situation (i.e., at − 1 min relative to the TSST). Additionally, non-adherent participants whose missing values exceed 25% of the data will also be excluded from the analysis. In the next step, Kolmogorov–Smirnov tests will be conducted in order to check for normal distribution. If necessary, data will be log-, ln-, or inverse transformed to reduce skewness of biological data.

To analyze the data (i.e., to compare self-report measures as well as biological response and habituation indices between experimental groups), we will use separate analyses of covariance (ANCOVAs). Sex and BMI will be used as covariates in analyses of biological data, as these two variables have been repeatedly shown to be highly relevant for stress system activity [61, 62]. We will use the standard *p* < 0.05 criteria for determining if the ANCOVA and the post hoc test suggest that the results are significantly different from those expected if the null hypothesis were correct. The post-hoc Bonferroni test adjusts for multiple comparisons.

To investigate associations between primary psychological outcome measures and indices of biological stress measures, we will compute separate hierarchical linear regression models, regressing biological outcome measures onto psychological outcome variables. Again, sex and BMI will be included as covariates in these analyses. When examining state variables, the respective trait variable will be included as covariate in regression analyses.

We expect that certain psychological (e.g., emotion regulation, coping), demographic (e.g., age, gender, sex), and anthropometric (e.g., BMI) variables may be related to biological stress system activity. Therefore, we will test for relationships between these variables and primary outcome measures of biological stress responses in an exploratory fashion.

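### Eighteen biological indices that the intervention can affect are unranked primary outcomes, each tested at 0.05, with no control of error across them

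*Protocol article*

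**What the plan says.** All references are to the protocol article.

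- **Primary outcomes** opens with the questionnaires: "Primary outcomes will include self-reported measures of affect, appraisals of task-related stress, trait and state rumination, as well as trait and state self-compassion". It then adds: "Further primary outcomes will be response and habituation indices of biological stress measures for HPA axis, autonomic, and inflammatory responses". The markers listed are "cortisol, sAA, HR, HRV, plasma IL-6, cytokine expression rates of IL-6, IL-1β, NF-кB, IкB", which makes nine. No outcome is ranked above another.
- **Indices.** The same section says that "delta scores will be computed for the initial and repeated exposure to stress using peak values relative to baseline", so each marker has two response indices. Habituation is the first response minus the second, a third index.
- **Data preparation and statistical analysis** compares the groups in separate ANCOVAs, each judged at p < 0.05. The only adjustment is this: "The post-hoc Bonferroni test adjusts for multiple comparisons".
- **Power analysis** assumes one three-group test at alpha 0.05. On scope it says: "The analysis is limited to the reference biomarkers cortisol and sAA".
- **Psychological assessments during screening** is the only place that describes the trait scales: "Trait rumination will be assessed using a German version of the Response Style Questionnaire" and "To assess trait self-compassion, a German version of the Self Compassion Scale". The scales used during the sessions are the state versions.

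**The concern.** A primary outcome should identify the result on which the trial's main claim stands or falls. Here the main claim, that coping manipulation modifies habituation, can draw on nine habituation indices and nine session-2 responses. Each is tested at the full 5% level and none has precedence. A Bonferroni correction of the pairwise group comparisons after an ANCOVA does nothing about the number of ANCOVAs.

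The protocol also does not say which markers, or how many, must be significant for Hypothesis 7 or 8 to count as supported. This matters more than usual because the Randomization section acknowledges that the analyst knows the group assignments and relies on strict adherence to the pre-registered plan to limit bias. Strict adherence to a long unranked list does not prevent selective emphasis afterwards.

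The primary set is also out of step with the sample size. Seven of the nine primary markers have no planned power.

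**Working it through.** **1. The plan's own figure.** For a one-way F test with three groups, alpha 0.05 and noncentrality f² × N, the smallest balanced N with at least 80% power at f = 0.30 is 111 (power 0.803; the same N with two covariates). This reproduces the stated 37 per group. It does so only if the printed 0.30 is f; read as f², as printed, N would be 36. That is a separate matter. What counts here is that 111 is the size for one test at 0.05.

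**2. Counting the biological indices.**

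- Markers: 9. Indices per marker: 2 responses + 1 habituation = 3. Total 9 × 3 = 27.
- Session-1 responses: 9. Hypothesis 6 expects no group difference in these.
- Indices the intervention can affect: 27 − 9 = 18 (9 session-2 responses and 9 habituation indices).
- Indices bearing directly on Hypothesis 8: 9.

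These are minimum counts. The section on heart rate variability names two HRV parameters; using both turns 9, 18 and 27 into 10, 20 and 30.

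**3. Chance of at least one false positive if tests are independent:** 1 − 0.95^m.

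- m = 9: 1 − 0.95^9 = 0.370
- m = 18: 1 − 0.95^18 = 0.603

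**4. Allowing for dependence.** The tests are not independent: habituation is an exact function of the two responses, and markers may correlate. A null simulation used N = 111, an ANCOVA with two covariates, habituation computed as response 1 minus response 2, and 3,000 runs per scenario. The correlations are assumptions, not figures from the documents: 0.3 to 0.7 between sessions and 0 to 0.5 between markers.

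| Set of indices | Independent | Simulated range |
|---|---|---|
| 9 habituation | 37% | 27-38% |
| 18 (session-2 response and habituation) | 60% | 45-59% |

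The top of the first range slightly exceeds 37% through simulation error, so the independent figures are approximate upper values. Self-report tests would add to each row.

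**5. What control would cost in sample size (f = 0.30, 80% power).**

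| Strategy | Alpha per test | N needed | Power at N = 111 |
|---|---|---|---|
| First marker in a fixed sequence | 0.05 | 111 | 80% |
| Two primaries, Bonferroni | 0.025 | 132 | 71% |
| Nine habituation indices, Bonferroni | 0.05/9 = 0.0056 | 177 | 51% |
| All 27 indices, Bonferroni | 0.05/27 = 0.00185 | 210 | 37% |

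In a fixed sequence, the second marker can succeed only if the first does. If f = 0.30 holds for both, the chance that both succeed lies between 0.803 + 0.803 − 1 = 0.61 and 0.80, depending on their correlation.

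**The case against.** Several points on the other side are sound.

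- **The figure for all 27.** A reader might quote 1 − 0.95^27 = 75% as the risk of a false efficacy claim. The documents do not support that. Nine of the 27 are session-1 responses, where Hypothesis 6 predicts no difference; a chance finding there would count against a hypothesis, not as efficacy. The third index of each marker is also determined by the other two.
- **One marker is enough.** A reader might infer that any single significant marker would be declared a positive trial. No section says so. Hypotheses 7 and 8 predict an ordering of the groups, and the Hypotheses section expects it in all three biological systems. What stands is narrower: no rule says how many markers must agree, or which.
- **Trait scales.** A reader might see primary outcomes measured before randomisation as inflating the error rate. They do not. No hypothesis claims an intervention effect on traits (Hypothesis 4 names state measures and affect), and the analysis section already uses the trait scales as covariates. This is mislabelling.
- **Manipulation checks.** The Affect, Experimental setting and procedure, and Hypotheses sections already describe the repeated self-report measures as checks on the manipulation. The outcome list still calls them primary.
- **The pre-registered plan.** It is cited in two sections, is not shown, and may contain a hierarchy. But the protocol itself prints the significance rule and the adjustment as following that plan, so an unseen repair cannot be presumed.
- **Type of study.** This is foundational work in healthy adults with no immediate effect on patients. That lowers the consequences of a false positive but does not change the error rate.

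**Conclusion.** The concern holds for the 18 biological indices that the intervention can affect, and most clearly for the nine habituation indices. As printed, the testing rule does not control error across primary outcomes. The chance of at least one false positive is about 27-38% for habituation alone and about 45-59% for the 18, with independent-test values of 37% and 60%. Even the lowest figure is more than five times the nominal 5%.

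The ranges rest on the assumed correlations above. The count of 18 assumes that session-1 responses precede the intervention task, which is the order in which the procedure section tells it. The abstract places assignment immediately after the first stress test, so the timing of the later session-1 samples should be confirmed; if any fall after the task, the count rises. That trait scales are measured only at screening rests on the text, because the schedule table is not shown.

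**What to change.** Before any data are analysed:

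1. Make habituation of cortisol and of sAA the primary outcomes, tested in a pre-specified fixed sequence at 0.05. The order is the sponsor's choice; the power analysis treats both as reference markers.
2. Make the remaining biological indices secondary, with inflammatory habituation as the key secondary family, under Holm or false-discovery-rate control across markers.
3. Treat session-1 responses as a pre-intervention comparability check.
4. List affect, appraisal and state scales as manipulation checks, and trait rumination and trait self-compassion as baseline covariates.
5. If the pre-registered plan already holds a hierarchy, state it in the protocol.

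The cost is wording in the protocol, the registry entry and the analysis plan. N = 111 is unchanged for the first marker in the sequence; power for the second is somewhat lower, as shown above. The study section on status and timeline rules out preliminary analyses, so the change can be made before results are seen. The real loss is that inflammatory markers, which Summary and objective singles out as a particular aim, give up primary status, although no power was planned for them.

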#### Secondary outcomes

Secondary outcomes will be psychological (e.g., emotion regulation, coping), demographic (e.g., age, gender, sex), and anthropometric (e.g., BMI) variables. Associations between primary and secondary outcomes will be analyzed in an exploratory fashion.

### Hypotheses

By increasing either ruminative or self-compassionate thoughts among healthy young adults, the intervention programs are expected to affect the regulation of occurring emotions as expressed by the responsiveness of biological systems during repeated stress exposure.

To check whether the experimental manipulations are successful on a psychological level, self-report measures will be assessed repeatedly over the course of each experimental session and are expected to change over the course of experimental sessions 1 and 2. Specifically, we hypothesize that stress will elicit changes in affect scores and stress appraisals, whereas the two intervention programs are expected to induce changes in affect, self-compassion and rumination, which will be stronger than in the control group (no intervention). Furthermore, we expect these variables to predict indicators of biological stress system activity.

Hypothesis 1: Independent of experimental session and group, stress will elicit significant increases of negative affect and stress appraisals as well as decreases of positive affect.Hypothesis 2: At experimental session 1, stress-induced changes of positive and negative affect and stress appraisals will be indifferent between participants from intervention groups 1 (rumination) and 2 (self-compassion) as well as participants from the control group (no intervention).Hypothesis 3: At experimental session 2, stress-induced decreases of positive affect as well as increases of negative affect and stress appraisals will be strongest in participants from intervention group 1 (rumination) and lowest in participants from intervention group 2 (self-compassion).Hypothesis 4: Increases in state self-compassion and positive affect from pre- to post-intervention will be strongest in intervention group 2 (self-compassion), and increases in state rumination and negative affect will be strongest in intervention group 1 (rumination).

Furthermore, we expect significant responses of biological stress system activity in all experimental groups at each experimental session. Specifically, we expect responses of biological stress system activity to be similar at experimental session 1 and participants from intervention group 2 (self-compassion) to show stronger habituation of stress system activity compared to intervention group 1 (rumination) or the control group (no intervention).

Hypothesis 5: Independent of experimental session and group, stress elicits significant responses of biological stress system activity.Hypothesis 6: At experimental session 1, responses of biological stress system activity will be indifferent between participants from intervention groups 1 (rumination) and 2 (self-compassion) as well as participants from the control group (no intervention).Hypothesis 7: At experimental session 2, responses of biological stress system activity will be strongest in participants from intervention group 1 (rumination) and lowest in participants from intervention group 2 (self-compassion).Hypothesis 8: Habituation of biological stress system activity will be lowest in participants from intervention group 1 (rumination) and strongest in participants from intervention group 2 (self-compassion).Hypothesis 9: Self-compassion and positive affect will predict lower biological responses to repeated stress, whereas rumination, negative affect, and stress appraisals will predict higher biological responses to repeated stress.Hypothesis 10: Self-compassion and positive affect will predict stronger habituation of biological stress system activity to repeated stress, whereas rumination, negative affect, and stress appraisals will predict lower habituation of biological stress system activity to repeated stress.

We expect these changes to occur among markers of the HPA axis, the autonomic system, as well as the inflammatory system.

Associations of biological stress system activity with other psychological variables (e.g., emotion regulation, coping) as well as demographic (e.g., age, gender, sex) and anthropometric (e.g., BMI) variables will be tested in an exploratory fashion.

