## Methods

### Study design

The study is designed as a randomized controlled, single-center, and single-blinded trial, in which participants will be randomly assigned to one of two intervention groups (rumination vs. self-compassion) or a control condition (see “Randomization”) with an allocation ratio of 1:1:1. The study employs a superiority trial design, aiming to determine whether one of the two cognitive coping interventions is more effective in modifying the responsiveness and habituation of biological stress systems compared to the control condition. The design encompasses repeated measurements of each group, i.e., each group will undergo two experimental sessions (t1 and t2) comprising stress test exposures, and within each experimental session, repeated biological and psychological outcome assessments will take place (see Table 1).

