### Tasks and interventions

#### Intervention group 1: rumination

According to the Response Styles Theory [21], rumination is described as repetitive thought process focused on the causes, consequences, and symptoms of negative affect, which may generally cause maintenance and amplification of depressive symptoms. Furthermore, Clark and Wells [22] describe rumination that specifically occurs after psychosocially stressful events (post-event rumination) as persistent processing or reflection about a previous social interaction.

As has been revealed by previous research, rumination is generally associated with indicators of lower psychological well-being, as it predicts the occurrence of future depressive episodes [23]. Additionally, individuals who strongly ruminate about prior stressful events exhibit dysfunctional biological adaptation mechanisms, including higher cortisol responses to acute stress [24], and sustained activation of the HPA axis and the inflammatory system [25]. Preliminary work has also revealed associations between stressor-related rumination and increased stress-induced responses of HPA axis activity to repeated acute stress, suggesting that rumination may impair the habituation of biological stress system activity [14]. Due to the persistent and passive focus on negative emotions in stressful situations as well as the impaired ability to adequately biologically adapt to acute and repeated stress, rumination is thus considered to have detrimental effects on long-term health.

As demonstrated by multiple studies, rumination can be experimentally induced, which affects the activation of the HPA axis and the inflammatory system [25, 26]. An analysis with preliminary data reveals that stressor-related rumination can be induced by a short-term writing intervention which leads to a reduction of HPA axis habituation [20]. Analogous to this experimental approach, the planned study aims to manipulate rumination as coping mechanism to gain insight into whether it may lead to maladaptive biological adaptation. To this end, the first intervention is designed to experimentally induce rumination by instructing participants to ruminate about their first stress exposure and, in particular, about their negative feelings and to write down their thoughts.

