### Conclusions

Our study will expand our current knowledge about the modifiability of biological stress and immune response patterns that are known to play a crucial role in the pathway linking stress and disease [12]. Specifically, by increasing indices of habituation to repeated stress exposure, beneficial effects of cognitive–behavioral techniques for physical health will be made visible. Overall, the findings will have important implications, especially in the context of psychotherapeutic stress management programs.

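### The ordered hypotheses have no matching test: no claim is tied to a pair of arms, so a self-compassion vs rumination difference could be read as a self-compassion benefit

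*Protocol article*

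**What the plan says.** All references are to the protocol article; the pre-registered analysis plan that it cites is not shown.

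- **Summary and objective** anticipates two separate effects: self-compassion promotes habituation and rumination impedes it.
- **Study design** sets a superiority aim against control: "whether one of the two cognitive coping interventions is more effective in modifying the responsiveness and habituation of biological stress systems compared to the control".
- **Hypotheses**, in the text before Hypothesis 5, expects self-compassion participants "to show stronger habituation of stress system activity compared to intervention group 1 (rumination) or the control group (no intervention").
- **Hypotheses, Hypothesis 8** says habituation "will be lowest in participants from intervention group 1 (rumination) and strongest in participants from intervention group 2 (self-compassion"), which leaves control in the middle. Hypotheses 3 (affect and appraisal) and 7 (biological response) name the same two arms as extremes at session 2.
- **Data preparation and statistical analysis** plans separate ANCOVAs and applies p < 0.05 for "determining if the ANCOVA and the post hoc test suggest that the results are significantly different" from the null, with a Bonferroni post hoc test. It names no planned contrast and no deciding pair.
- **Power analysis** sizes the trial for three groups: "Power analyses revealed a sample size of *N* = 111 (*n* = 37" per arm), "using an effect size of *f*^2^ = 0.30, *α* = 0.05, 1-*β* = 0.80, number of groups = 3".
- **Conclusions** expects that "by increasing indices of habituation to repeated stress exposure, beneficial effects of cognitive–behavioral techniques for physical health will be made visible".

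**The concern.** The omnibus F tests whether all three means are equal. It cannot separate a benefit of self-compassion from harm by rumination, yet the article anticipates both as distinct effects. Only self-compassion vs control speaks to the first and only control vs rumination to the second. Self-compassion vs rumination differs if either effect is present.

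The article gives three criteria that do not match: better than control (Study design), better than rumination or control (text before Hypothesis 5), and best of all three (Hypothesis 8). The test section does not choose between them.

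Rumination acting alone is a realistic scenario. The effect sizes in the Power analysis (d = 0.81 for cortisol, d = 0.67 for sAA) come from a preliminary study. The rumination section describes that same study as showing that "stressor-related rumination can be induced by a short-term writing intervention which leads to a reduction of HPA axis habituation". For self-compassion, the article cites trait associations with stress responses and effects of training on mood, well-being and glucose, but no experimental effect on habituation.

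At stake is the health-promotion conclusion, which depends on the self-compassion arm. The Randomization section also says that the analyst knows the allocation and that adherence to pre-set criteria is the safeguard, so the criteria should not be open to choice.

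**Working it through.** **Inputs from the article:** three arms, 1:1:1, 37 evaluable per arm, alpha 0.05, d = 0.67 and 0.81.

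**Assumptions:** normal outcomes with unit residual SD; two covariates (sex, BMI) taking 2 error df, so df = 111 − 3 − 2 = 106; Bonferroni over the three pairs (two-sided 0.05/3); two-sided tests. d = 0.50 is added as a smaller effect.

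**1. The plan's own figure.** Omnibus F with noncentrality N·f². At f = 0.30, N·f² = 111 × 0.09 = 9.99 and power is 0.803, so N = 111 is reproduced. Taking the printed f² = 0.30 literally gives N = 36. The figure is therefore for the three-group omnibus test at f = 0.30.

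**2. Only rumination acts.** Means (rumination, control, self-compassion) = (−d, 0, 0), 37 per arm, simulated with 200,000 runs or more per scenario:

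| d | Omnibus significant | Omnibus and self-compassion > rumination (Bonferroni) | Self-compassion > control (Bonferroni) |
|---|---|---|---|
| 0.50 | 58% | 39% | 0.8% |
| 0.67 | 84% | 67% | 0.8% |
| 0.81 | 95% | 85% | 0.9% |

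Hand check at d = 0.67: the pair's noncentrality is d·√(n/2) = 0.67 × √18.5 = 2.88 against a critical t of 2.43, giving power 0.67. With 40 per arm the middle column is 42%, 71% and 88%.

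**3. Is Bonferroni needed after a significant F?** For one outcome and three groups:
- If all three means are equal, the F test itself holds the error at 5%.
- If exactly two are equal, only one pairwise null is true, and testing it at 0.05 holds the error at 5%.
- If all differ, no pairwise null is true.

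Unadjusted pairs after a significant F therefore already control the familywise error. A claim that requires both contrasts to be significant needs no adjustment either.

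**4. What the adjustment costs.** Equal steps s at f = 0.30: f² = 2s²/3, so s = 0.30 × √1.5 = 0.367 SD. 37 per arm:

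| Scenario | Result | Bonferroni | 0.05 after significant F |
|---|---|---|---|
| Equal steps, f = 0.30 | Self-compassion > control | 20% | 34% |
| Equal steps, f = 0.30 | Both steps | 1.1% | 5.6% |
| Only self-compassion acts, d = 0.67 | Self-compassion > control | 67% | 77% |
| Only rumination acts, d = 0.67 | Self-compassion > control (false) | 0.8% | 2.5% |

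In the last row, 2.5% is one direction of a two-sided 0.05 test, so the error stays at its nominal level.

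**5. Size needed for the order.** 80% power for both steps, each at two-sided 0.05, needs about 158, 85, 48 or 33 per arm at 0.367, 0.50, 0.67 or 0.81 SD per step.

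**The case against.** A reader might infer that the plan counts any significant pair as success. It does not say so. It leaves the deciding pair open, so the 39% to 85% show how often an ambiguous result would arise, not how often a written rule would err.

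The word 'or' may simply mean 'than either'. Hypothesis 8 is stricter and already requires self-compassion to be strongest. The Abstract and Study design name control as the comparator, and the Control group section explains that it is there so that changes can be attributed to the specific strategy. The post hoc output would contain self-compassion vs control, and in the scenario above that pair would almost always fail visibly. This stands: the misreading is possible, not built in.

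It would also be wrong to call the 39% to 85% an inflated type I error. In that scenario self-compassion and rumination truly differ, so rejecting their equality is correct. The error would lie in what is then concluded about self-compassion.

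The 'or' sentence concerns habituation, so it bears on Hypothesis 8. Hypotheses 3 and 7 share only the lack of a test that matches their order.

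Finally, the pre-registered plan may name the contrasts. That would settle the analysis, but the article's three criteria would still disagree, and its stated post hoc method would need to be aligned.

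**Conclusion.** The point holds in a limited form. The article states an order and two directional claims, tests them with an undirected F test and a Bonferroni post hoc step, and ties neither claim to a contrast. The prose criterion for habituation is looser than Hypothesis 8. If only rumination acts, a result that could be taken as support for self-compassion appears in 39% to 85% of trials for d from 0.50 to 0.81, although the contrast that would justify such a claim is significant in under 1%.

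Separately, the stated Bonferroni step gives up power without need: 20% against 34% for self-compassion vs control at the planned effect with equal steps.

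These figures assume 37 evaluable per arm, normal outcomes and effects in residual SD units, and they apply to one outcome at a time. The equal-step spacing is an assumption, because the article gives no effect for each arm. The article does not support the stronger reading that a self-compassion claim would necessarily be made from the rumination pair.

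**What to change.** 1. **Hypotheses, text before Hypothesis 5:** change 'or' to 'and', so that it agrees with Hypothesis 8.
2. **Data preparation and statistical analysis:** replace the Bonferroni post hoc step with two planned contrasts from the same ANCOVA, each tested at two-sided 0.05 only after a significant omnibus F:
   - self-compassion vs control, the sole basis for saying that self-compassion promotes habituation;
   - control vs rumination, the sole basis for saying that rumination impedes it.
3. Claim the full order in Hypotheses 3, 7 and 8 only if both contrasts are significant in the predicted direction.
4. Report self-compassion vs rumination, but let it support neither claim against control.
5. Use this one procedure throughout. If the separate claims used Holm and the order claim used unadjusted tests, p-values of 0.03 and 0.04 would support the order while denying both of its parts.
6. **Power analysis:** state that N = 111 is sized for the omnibus test, and that at f = 0.30 with equal steps power is about 34% for self-compassion vs control and about 6% for both steps.
7. If the pre-registered plan already names contrasts, align the article with it.

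**Cost:** a few sentences, with the same model, data and sample size. The self-compassion claim becomes harder to earn than through the rumination pair, and the low power for the full order has to be disclosed.
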